## Abstract

**Background:**

Oral cancer is a major health problem worldwide. The 5-year survival rate ranges from 30-60%, and has remained unchanged in the past few decades. This is mainly due to late diagnosis and high recurrence of the disease. Of the patients who receive treatment, up to one third suffer from a recurrence or a second primary tumor. It is apparent that one major cause of disease recurrence is clinically unrecognized field changes which extend beyond the visible tumor boundary. We have previously developed an approach using fluorescence visualization (FV) technology to improve the recognition of the field at risk surrounding a visible oral cancer that needs to be removed and preliminary results have shown a significant reduction in recurrence rates.

**Method/Design:**

This paper describes the study design of a randomized, multi-centre, double blind, controlled surgical trial, the COOLS trial. Nine institutions across Canada will recruit a total of 400 patients with oral severe dysplasia or carcinoma *in **situ *(N = 160) and invasive squamous cell carcinoma (N = 240). Patients will be stratified by participating institution and histology grade and randomized equally into FV-guided surgery (experimental arm) or white light-guided surgery (control arm). The primary endpoint is a composite of recurrence at or 1 cm within the previous surgery site with 1) the same or higher grade histology compared to the initial diagnosis (i.e., the diagnosis used for randomization); or 2) further treatment due to the presence of severe dysplasia or higher degree of change at follow-up. This is the first randomized, multi-centre trial to validate the effectiveness of the FV-guided surgery.

**Discussion:**

In this paper we described the strategies, novelty, and challenges of this unique trial involving a surgical approach guided by the FV technology. The success of the trial requires training, coordination, and quality assurance across multiple sites within Canada. The COOLS trial, an example of translational research, may result in reduced recurrence rates following surgical treatment of early-stage oral cancer with significant impacts on survival, morbidity, patients' quality of life and the cost to the health care system.

**Trial Registration:**

Clinicaltrials.gov NCT01039298

## Background

Oral cancer is a major health problem worldwide, accounting for 274,000 new cases and 145,000 deaths annually [1]. Although it occurs at a site that is easily accessible for examination it is often diagnosed at an advanced stage, with 5-year survival rates ranging from 30-60%, depending on the global locale. Treatment of early stage squamous cell carcinoma is an essential component of effective oral cancer management; a recent large (~190,000) randomized trial of a screening program showed the mortality rate ratio between intervention and control groups was 0.79 [95% CI 0.51 - 1.22] [2]. However, even with treatment there are high rates of second oral malignancies, with up to a third of these patients suffering a recurrence or a second primary [3,4]. There has been extensive research in the importance of examining the field surrounding oral cancers for risk assessment and management of this disease [5-7]. Using molecular technology, it is becoming increasingly apparent that genetically altered cells are often widespread across the mucosa of patients with oral cancer, extending into clinically and histologically normal tissue, and that these cells can drive the process of field cancerization. Recognizing this, surgeons try to remove oral squamous cell carcinomas (SCC) with a significant margin of surrounding normal-looking oral mucosa. However, the occult disease varies in size and a wealth of evidence suggests that it frequently extends beyond the tumor clearance area [5-8]. This extension may be responsible for the high rate of cancer recurrence at the primary site (10-30% of SCC cases) [9-11]. Taking margins that are too large can result in over-cutting (causing severe cosmetic and functional morbidity) and margins that are too small may leave cancerous tissue behind, as evidenced by frequent positive surgical margins and high local and regional recurrence - a failure of the 'best practice'.

Our research team has developed an approach using fluorescence visualization (FV) technology, which improves the recognition of the field at risk surrounding a visible oral cancer [12,13]. Our preliminary results show that using FV to define the field at risk for surgical resection can result in a marked reduction in recurrence rates at 3 years (0/38 vs. 7/22) [14]. Our goal in this study is to rigorously evaluate and validate the effectiveness of FV-guided surgeries compared to white light in a multicentre pan-Canadian randomized control study.

## Objective

The trial has 4 objectives. The primary objective is to determine the effectiveness of FV-guided surgery in reducing local recurrence after surgical excision of severe dysplasia or cancer of the oral cavity. Secondary objectives include 1) To collect molecular and phenotypic evidence in margins to test if FV produces a shift in surgical field, sparing normal tissue while catching high-risk occult tissue; 2) To collect relative cost-effective evidence of the two arms in both the cost per avoided recurrence and the cost per quality-adjusted life years gained; and 3) To develop a knowledge translation (KT) strategy that will foster the dissemination of FV-guided surgery across Canada and globally.

## Methods/design

### Study design

The COOLS trial is a multicentre, double blind, randomized controlled study, comparing FV- guided surgery (experimental arm) to conventional white light (WL)-guided surgery (control arm). See Figure 1 for the schema of the study.

**Figure 1 F1:**
[figure not shown]
**Trial schema**. A total of 400 subjects (240 invasive squamous cell carcinoma and 160 severe dysplasia or carcinoma in situ) will be randomized equally into FV-guided surgery (experimental arm) or white light-guided surgery (control arm). The primary endpoint is a composite of recurrence at or 1 cm within the previous surgery site with 1) the same or higher grade histology compared to the initial diagnosis (i.e., the diagnosis used for randomization); or 2) further treatment due to the presence of severe dysplasia or higher degree of change at follow-up.

This study has been approved by the human research ethics committees at each of the participating institutions. Any future amendments to the study protocol will be submitted to each committee for approval. The trial has been registered at Clinicaltrials.gov (NCT01039298).

### Sample size

A total of 400 subjects (240 invasive squamous cell carcinoma and 160 severe dysplasia or carcinoma *in situ*) will be randomized from 9 centres across Canada (from west to east): Vancouver, British Columbia; Calgary and Edmonton, Alberta; Winnipeg, Manitoba; Toronto (Sunnybrook Hospital), London, and Ottawa, Ontario; Montreal (McGill University Health Centre), Quebec; Halifax, Nova Scotia.

### Target population

The study is open to patients with high-grade preinvasive (severe dysplasia/carcinoma *in situ*) or invasive squamous cell carcinoma (T1 or T2) of the oral cavity.

### Inclusion Criteria

Patients with disease localization at oral anatomical sites that can be visualized using both white light and fluorescence visualization device (this includes ICD-10 site codes: C02.0-C06.9); patients with a clinical diagnosis of N0 or N1 as confirmed by CT scan, with the latter undergoing neck dissection; or patients with resectable locally recurrent disease diagnosed with severe dysplasia or higher grade, provided that they are at least 6 months post-treatment (this time frame will allow resolution of artefacts produced by treatment that could impact on tumor or lesion visualization).

### Exclusion Criteria

Patients with concurrent non-oral malignancy diagnosed within the past 3 years (patients with non-melanoma skin cancer or lymphoma that lie outside of the head and neck region are included); patients with evidence of distant metastasis, as determined by CT and X-ray at the time of recruitment; patients with illnesses that could preclude standard diagnostic tests and post-surgery follow-up; and patients with lesions located at the base of tongue (C01) or tonsil (C09), as these sites are not readily assessable to FV.

All patients will provide written informed consent for study participation.

### Key steps

#### Patient recruitment

Site surgeons will identify potentially eligible patients and briefly introduce the study to the patient (see key steps in Figure 2). The local site coordinator will be informed and will contact the patient to arrange an appointment to discuss the study and for a pre-surgery assessment. As part of that eligibility assessment, all patients with squamous cell carcinoma will have a CT scan from skull base to chest as a baseline to confirm the clinical nodal status and the absence of the upper alimentary and respiratory tract and lung metastasis or second primary tumor. Upon verifying all the eligibility criteria, the study coordinator will obtain informed consent from the eligible and interested patients.

**Figure 2 F2:**
[figure not shown]
**Flow chart of key steps and the involvement of key personnel in each steps and site coordinator's role**.

#### Pre-surgery assessment

Prior to the assessment, the site coordinator will assist the patient to complete a set of study questionnaires covering socio-demographic factors, risk factors, comorbidity and family cancer history. Quality of life will be assessed with the EQ-5D [15,16], the Functional Assessment of Cancer Therapy Head and Neck Module (FACT-H&N)[17,18] and the Speech Handicap Index, a specific tool for the measurement of speech pathology. [19]

The lesion undergoing surgery will be assessed by a trained FV Specialist (FVS) using both WL and FV. The FVS will be either a dental specialist or a head & neck surgeon who will not be performing the surgery for the patient. With the assistance of the site coordinator, digital images will be obtained of the lesion under both conditions and lesion size and location will be recorded on the case report form (CRF). Both the images and the CRF will be uploaded to the trial's web-based database.

The FV assessment will be performed with an autofluorescence imaging device, marketed as the VELscope^®^, (LED Dental Inc., White Rock, British Columbia, Canada), using protocols described in Poh *et al*. [12] The examination is performed under reduced room lighting and involves the inspection of the entire oral mucosa in the same manner as the conventional intraoral examination, with special attention to the lesion site. Tissue that show a reduction in the normal pale green, appearing as dark patches, will be categorized as FV positive (FVpos). Lesions that retain the normal green autofluorescence under FV are classified as FV negative (FVneg). Both WL and FV digital images of the lesion will be recorded prior to randomization.

#### Intervention (Surgery)

At the time of surgery the operating surgeon will outline the boundary of the clinically visible lesion under white light. The FVS will take an image (***Image 1***); measure its size; and record data on the surgical tracking sheet.

##### a. If this is a FV-guided surgery (experimental arm)

With the operating room (OR) lights off, the FVS will use the VELscope Vx to examine the lesion and outline the FV change using a green Sharpie pen. After the FV positive boundary is outlined, images (***Image 2***) are taken in the dark to demonstrate the distance between FVL and clinical outline.

With the OR light back on, the FVS will measure the distance from FV boundary to the clinical boundary in 4 directions, and record this on the surgical tracking sheet. The site surgeon will outline a 10 mm surgical boundary around the clinically visible tumor and FV boundaries, whichever is wider. The FVS will take images (*Image 3*) under both FV and WL and record if there is any anatomical restriction for the placement of the standardized surgical boundary.

##### b. If this is a WL- guided surgery (control arm)

With the light off, the FVS will use the VELscope VX to examine the lesion and draw an outline on top of the surgeon's clinical boundary using a green Sharpie pen. After this step, the FVS will take another set of images (*Image 2*). In this case, the 2 outlines will be identical and this will be recorded on the surgical tracking sheet. The surgeon will outline a 10 mm surgical boundary around the clinical/FV boundary. The FVS will take images (*Image 3*) under both FV and WL and record if there is any anatomical restriction for the placement of the standardized surgical boundary.

The operating surgeon will remain outside the OR while the FVS marks the boundaries. Although it is unlikely the surgeon will remain blinded once the two markings are made, any deviation from the marked boundary will be recorded to allow assessment of deviation from the protocol.

Blood samples (5 ml in SST and 12 ml in EDTA tubes) will be collected at this time prior to the surgery. The tumor will then be resected and oriented using a suture for the anterior or right orientation. This will be indicated on the routine pathology requisition form to help the SP to orient the resected tissue. The specimen will be wrapped in a piece of cold saline gauze and kept on ice during transfer to the Pathology Department for processing.

The Site Pathologist (SP) will either use the tracking sheet or a print-out of the digital image of the excised tissue to record the tissue blocking. One-week after the diagnosis has been determined all the H&E sections will be sent to the Central Histology Review committee for histological review. If there is disagreement on the assessment between the site pathologist and the review committee, a teleconference will be arranged in order to discuss and achieve consensus. The site coordinator will upload all images, surgical and pathological CRFs and key information from pathology reports into the study database.

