### Randomization

Stratified randomization will be employed. Two stratification factors will be applied: 1) institution and 2) histological grade of the primary lesion (severe dysplasia and carcinoma *in situ *or invasive squamous cell carcinoma).

A randomization program has been written specifically for this trial ([name]). According to the information collected, the central database manager under the supervision of the study biostatistician ([name]) will perform the randomization. Within each stratum, the minimization algorithm will be used to achieve balanced randomization with respect to other prognostic factors, including surgeon, gender, age, smoking history, and lesion anatomical sites. [20]

The randomization will be done 1 - 2 days prior to surgery. Only the FVS will be notified of the result. The patient, research staff, operating surgeon, and the pathologist are not aware of the assignment. The allocation list will be held by the study database manager; this individual is not involved in patient care or recruitment. The allocation will only be revealed in the event of an emergency medical situation.

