## Statistical design and analysis

The trial data will be analysed by the biostatistician ([name]) who will be blinded to the treatment allocation (masked as Treatment A or Treatment B) during the study period.

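### The surgical tracking sheet and marked images reveal the arm to the site coordinator, and to the site pathologist where the sheet is used, although both are declared unaware of the assignment

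*Protocol article*

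**What the plan says.** All places are in the protocol article.

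- **Randomization.** Knowledge of the allocation is confined to one role: "Only the FVS will be notified of the result". The text then lists those who are blind: "The patient, research staff, operating surgeon, and the pathologist are not aware of the assignment".
- **Intervention, FV-guided arm.** The FV specialist is to "measure the distance from FV boundary to the clinical boundary in 4 directions, and record this on the surgical tracking sheet". Image 2 is taken to show the gap between the two outlines.
- **Intervention, WL-guided arm.** The FV specialist traces over the surgeon's outline: "In this case, the 2 outlines will be identical and this will be recorded on the surgical tracking sheet".
- **Same section, specimen handling.** "The Site Pathologist (SP) will either use the tracking sheet or a print-out of the digital image of the excised tissue" when recording how the tissue was blocked. Then: "The site coordinator will upload all images, surgical and pathological CRFs and key information from pathology reports into the study database".
- **Same section, concession.** The text accepts that one person, the operating surgeon, is unlikely to stay blind once the markings are made. It makes no such concession for the coordinator or the pathologist.
- **Biostatistician.** Randomization is performed by "the central database manager under the supervision of the study biostatistician". Statistical design and analysis says that the trial data are analysed by a biostatistician "who will be blinded to the treatment allocation (masked as Treatment A or Treatment B) during the study period".

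**The concern.** A trial described as double blind names the people who are unaware of the assignment, and then sends two of them documents from which the assignment can be read. The control-arm procedure was built to hide the arm: the light goes off, a second outline is drawn, and the same images are taken. What is written down afterwards undoes part of that, because the entries on the sheet differ by arm.

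The outcome most exposed is failure of the first pass, the first secondary endpoint. It counts a positive margin at either the intraoperative or the paraffin assessment, and the site pathologist makes the local diagnosis before central review. A second possible route runs through the consensus teleconference. When the site pathologist and the central review committee disagree on the surgical specimen, they discuss the case until they agree. According to the Discussion, the central committee also adjudicates the trial endpoint from follow-up biopsies. A site pathologist who knows the arm could therefore disclose it to a body that is meant to stay blind.

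**Working it through.** The plan states no figure on this point, so there is none to reproduce. The check sets the statements side by side, followed by one illustration.

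**Step 1: does the sheet reveal the arm?** The FV arm gets four distances. The control arm gets a note that the outlines are identical. Outlines that differ can arise only in the FV arm, because in the control arm the second outline is drawn on top of the first. Fidelity of the intervention says that pathologists and project coordinators at each site are trained in all study procedures, so they can be expected to understand these entries.

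**Step 2: who handles it?**

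| Person | Declared status | What the procedures give them |
|---|---|---|
| Site coordinator | Unaware, reading the coordinator as research staff | All images, including Image 2, and the surgical case report forms |
| Site pathologist | Unaware | The tracking sheet, as one of two options for recording blocking |
| Operating surgeon | Unaware, but loss of blinding conceded | The markings themselves |
| Biostatistician | Blinded, arms masked as A and B | Supervision of the randomization; no list and no A/B key mentioned |

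The coordinator's exposure is part of the routine for every patient. The pathologist's depends on which option is used and on which sheet is meant. The surgical tracking sheet is the natural reading, because it is the only one named in the surgery sections. The lesion tracking sheets appear later and belong to follow-up visits.

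**Step 3: when?** Blocking comes before the sections are cut, so a pathologist who uses the sheet has it before the paraffin reading. Nothing shows that the sheet is at hand when an intraoperative margin is called.

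**Step 4: how revealing is the sheet alone?** This is an illustration. Allocation is 1:1 (Abstract). Let q be the share of FV-arm patients whose two outlines coincide. The article gives no value, so q is assumed. Assume also that the entry for such a patient looks the same as a control-arm entry, which favours blinding. A reader of the sheet guesses FV when the outlines differ and WL when they coincide.

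- P(FV | outlines differ) = 1
- P(WL | outlines identical) = 0.5 / (0.5 + 0.5q) = 1/(1 + q)
- P(correct guess) = 0.5 × 1 + 0.5 × (1 − q) = 1 − q/2

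| q (assumed) | P(WL given identical) | Correct guesses |
|---|---|---|
| 0 | 1.00 | 100% |
| 0.10 | 0.91 | 95% |
| 0.25 | 0.80 | 87.5% |
| 0.50 | 0.67 | 75% |

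Chance alone gives 50%. Even if half of the FV-arm outlines coincided, the sheet would still inform a guess.

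**The case against.** The strongest reply is that the pathologist's exposure is conditional. The sheet is one of two options, it is not named in full, and the details of blocking are in a training manual that is not shown. This limits how far the point goes for the pathologist. It does not remove the contradiction, because the article itself offers the sheet and nothing in it restricts that use. It also does not touch the coordinator.

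A second reply is that the markings may still be visible on the specimen, and therefore on a print-out of its image. Splitting a form would then not fully restore the pathologist's blinding. This is fair, and it is why the blinding statement must change as well as the paperwork.

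Four stronger readings are tempting, and the article does not support them.

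- *The blinded biostatistician receives the allocation.* The database manager performs the randomization and holds the list, and the arms are masked. Supervising the program is not the same as seeing assignments. Names are removed, so it is likely but not certain that both sections mean one person. No text puts the FV distances in the analysis file.
- *The intraoperative margin reading is biased.* The article does not say who makes that reading, or that the sheet is then available. The Discussion also has the central committee review all margin pathology of the surgical samples.
- *The coordinator's knowledge colours quality-of-life answers or interim reports.* The only stated help with questionnaires is at the pre-surgery assessment, where the images are recorded before randomization. At follow-up the coordinator is said only to upload the data, and interim results go to the monitoring board.
- *Primary endpoint adjudication is unblinded.* The adjudicating committee is declared blinded. The teleconference is a possible leak, not a demonstrated one.

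**Conclusion.** The point holds in a limited form. As written, the stated blinding of the site coordinator does not hold, and that of the site pathologist does not hold where the tracking sheet is used. It rests on two readings, both natural but not explicit: that the coordinator counts as research staff, and that the tracking sheet offered to the pathologist is the surgical one.

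The outcome most exposed is the secondary first-pass margin endpoint. The effect on it cannot be sized, because the article gives neither a first-pass failure rate nor the share of cases in which the sheet is used. The 75 to 100% range of correct guesses describes how revealing the sheet is under assumed q from 0.50 to 0. It does not measure bias. The point merits correction because the remedy is nearly free. It does not call the primary analysis into question.

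**What to change.** 1. Delete the option for the site pathologist to use the tracking sheet. Supply a blocking diagram without FV data instead.
2. Put the FV distances, the note on identical outlines and Images 2 and 3 on a separate form and in an access-restricted folder, uploaded by the FV specialist instead of the site coordinator. Access must still allow the central review of boundary drawings described under Fidelity of the intervention.
3. Restate in Randomization who may not remain blind. Outlines may still be visible on the specimen or on its printed image, so the pathologist's blinding should not be claimed without qualification.
4. As a minor clarification, state that the biostatistician who supervises the randomization program sees neither individual assignments nor the A/B key.

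The cost is one split form, a change of database access rights and a blinding statement that reads less favourably. No extra staff are needed.
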